## Abstract

**Background:**

Non-small cell lung cancer is the most common cause of cancer death worldwide, highlighting the need for novel therapeutic concepts. In particular, there is still a lack of treatment strategies for the group of elderly and frail patients, who are frequently not capable of receiving standard therapy regimens. Despite comprising the majority of lung cancer patients, this group is underrepresented in clinical trials. This applies also to elderly and frail patients suffering from unresectable stage III NSCLC, who are unfit for chemotherapy, and, therefore, cannot receive the standard therapy comprising of radiochemotherapy and the recently approved subsequent durvalumab consolidation therapy. These patients often receive radiotherapy only, which raises the concern of undertreatment. The TRADE-hypo trial aims at optimizing treatment of this patient group by combining radiotherapy with concomitant durvalumab administration, thereby employing the immune-promoting effects of radiotherapy, and determining safety, feasibility, and efficacy of this treatment.

**Methods/ design:**

In this prospective phase II clinical trial, durvalumab therapy will be combined with either conventionally fractionated (CON-group) or hypofractionated (HYPO-group) thoracic radiotherapy. A safety stop-and-go lead-in phase will assess safety of hypofractionated radiotherapy with respect to severe pneumonitis in small patient cohorts before opening full enrollment. Tumor tissue, blood and stool samples will be collected before and during the study period to investigate the immunological mechanisms responsible for checkpoint inhibitor efficacy and immune-promoting effects of radiotherapy.

**Discussion:**

Preclinical data suggests that irradiation-induced immunogenicity can be further increased if applied in a hypofractionated setting, potentially boosting the expected synergistic effect with immune checkpoint inhibition in restoring the immune anti-tumor response. If proven safe and efficient, a hypofractionated radiation schedule can provide a considerably more practicable option for the patient. Taking into consideration the intend to develop a combination treatment strategy that can be made available to patients soon after proving to be efficient and the potentially elevated toxicity of a hypofractionated radiotherapy approach, this trial was designed as a two-trials-in-one design. An accompanying translational research program is planned striving to gain insights into the tumor-host biology and to identify suitable biomarkers to predict therapy response.

**Trial registration:**

Clinicaltrials.gov, NCT04351256. Registered 17 April 2020,

Eudra-CT, 2019–002192-33. Registered 24 October 2019,

## Background

Lung cancer is the most common cause of cancer death worldwide, with non-small cell lung cancer (NSCLC) representing 80–90% of cases [1, 2]. Improving therapeutic strategies is thus of imminent importance, especially considering elderly and frail patients. With a median age of about 70 years at diagnosis lung cancer clearly is a disease of the elderly, yet this group is underrepresented in clinical trials, and these patients are frequently not capable of receiving standard treatment protocols due to age- and tobacco-associated comorbidities [3–5].

In recent years, the advent of immunotherapy has paved the way for novel therapeutic concepts, including the combination of radiotherapy with immune checkpoint inhibition (e.g. Programmed cell death/ -ligand 1; PD-1/ PD-L1). This approach is of particular interest as it utilizes synergistic effects: While immune checkpoint inhibitors can restore the patients’ antitumor immunity through T cell activation, radiotherapy may further boost immune-mediated anti-cancer mechanisms by exposing tumor-associated antigens and by attracting both immunocompetent antigen-presenting cells and tumoricidal effector cells [6, 7]. Indeed, for patients with unresectable stage III NSCLC, the PACIFIC trial has revealed a profound clinical benefit treatment with the anti-PD-L1 monoclonal antibody durvalumab after chemoradiotherapy with remarkably low toxicities [8, 9]. As a result, sequential treatment with durvalumab after chemoradiotherapy has become the new standard treatment for locally advanced, unresectable NSCLC. However, about 20% of patients do not receive chemotherapeutic agents, presumably due to significantly higher rates of age- and comorbidity-related adverse events (AE) under chemoradiotherapy [5, 10]. Thus, elderly and frail patients often receive radiotherapy alone, raising the serious concern of undertreatment and the need for new therapeutic concepts [4, 5].

Considering the immune-promoting effects of radiotherapy, a combination with durvalumab therapy may improve response rates in these potentially undertreated patients. Moreover, if applied early, concomitant local radiotherapy with systemic immunotherapy may particularly increase control of distant micrometastases. Preclinical data suggest that irradiation-induced immunogenicity can even be further increased if applied in a hypofractionated setting with single doses ≥3 Gray (Gy), in line with a radiation dose-dependent abscopal effect [11–14]. While a hypofractionated radiation schedule is also considerably shorter and more convenient for the patient, safety of concurrent immunoradiotherapy is a concern, as both therapy modalities may cause severe pneumonitis.

In this prospective phase II clinical trial, we therefore aim to determine feasibility and treatment efficacy of durvalumab treatment combined with thoracic radiotherapy (TRT) in previously untreated NSCLC stage III patients unable to receive radiochemotherapy. Striving to develop a combination treatment strategy that, if proven safe and efficient, can be quickly made available to patients, a two-trials-in-one design was chosen that combines durvalumab with either conventionally fractionated (CON-group) or hypofractionated thoracic radiotherapy (HYPO-group). This study not only aims to increase the efficacy of radiotherapy by utilizing the immune-sensitizing effects elicited by PD-L1 inhibition, but will also provide biomaterials that will be analyzed with respect to immunological mechanisms responsible for checkpoint inhibitor efficacy and immune-promoting effects of radiotherapy as well as potential biomarkers.

## Methods/design

### Study design

The TRADE-hypo trial is a prospective, randomized, open-label, multicenter, phase II trial with a safety stop-and-go lead-in phase (Fig. 1). During the lead-in phase, patients in the HYPO-group, who will receive durvalumab in combination with hypofractionated thoracic radiotherapy, will be closely evaluated with regard to toxicity (defined as pneumonitis ≥ grade 3 within 8 weeks after radiotherapy) in small cohorts (*n* = 6) before proceeding with full enrollment into this arm (Fig. 2).

**Fig. 1 Fig1:**
[figure not shown]
Study design of the TRADE-hypo trial. Patients will be enrolled according to eligibility criteria and treated with either a hypofractionated TRT regimen (HYPO-group) or conventionally fractionated TRT (CON-group) in combination with durvalumab. For the HYPO-group, a safety stop-and-go phase with a 6 + 6 design precedes full enrollment. Whenever this arm is open for recruitment, patients will be allocated to this arm until the cohort is closed; whenever HYPO-arm is closed for Stop/ Go decision evaluation based on the toxicity assessment of this regimen 8 weeks after the end of TRT, patients are allocated to the CON-arm. When the study proceeds to expansion phase, patients will be allocated to treatment arms by randomization using “biased coin” algorithm. An efficacy interim analysis will be performed after 18 patients have been enrolled in each arm

**Fig. 2 Fig2:**
[figure not shown]
Cohort design of the safety stop-and-go lead-in phase (HYPO-group). The safety lead-in phase follows a 6 + 6 design in order to carefully evaluate the toxicity of the treatment in the HYPO-group with respect of the occurrence of a grade 3/4 pneumonitis (“event”) within 8 weeks after the end of TRT. Two events in the first six patients, two events in the first 12, or two events in the first 18 patients will result in termination of the HYPO-group (“Stop”). If no event is observed within the first two safety cohorts, i.e. the first 12 patients, the HYPO-arm will be opened for full enrollment with close toxicity assessment with respect to pneumonitis grade 3/4, and terminated as soon as two events are reported within the subsequent six patients (“Go*”). Full enrollment in the HYPO-arm will only take place if the criteria for the non-toxicity scenario are met, i.e. ≤ 1 event in *n* = 18 patients (“Go”)

### Study setting

The TRADE-hypo trial will recruit patients from 17 participating centers across Germany over a period of 20 months. Start of recruitment was planned for April 2020, but was delayed to May 2020 due to the Covid-19 pandemic. A full list of sites can be obtained at clinicaltrials.gov (NCT04351256).

### Study objectives

The primary objective of this study is to evaluate safety and tolerability of conventionally fractionated (CON-group) and hypofractionated (HYPO-group) TRT in combination with durvalumab in patients with unresectable stage III NSCLC unfit for chemotherapy. Moreover, efficacies of the two modes of radiotherapy will be evaluated with respect to response rates. Further parameters will be determined in order to assess efficacy, safety, and quality of life (QoL) in both treatment arms by recording incidence and severity of adverse events (AEs) as well as specific laboratory abnormalities.

Exploratory endpoints include assessment of vulnerability and analyses of tumor tissue, blood, and stool samples that are collected during the clinical trial with respect to treatment-induced changes and immune-related biomarkers.

### Characteristics of participants

A total of 88 patients will be included into this study. Patients potentially eligible for trial inclusion will be approached and asked to participate as they present in the clinic. Before a patient’s participation in the clinical study, the investigator must obtain written informed consent.

Each participant must be eligible regarding all inclusion and exclusion criteria set for this trial (Table 1). Key inclusion criteria include diagnosis of unresectable stage III NSCLC and non-feasibility of sequential chemoradiotherapy due to increased (oxygen-independent) vulnerability as reflected by fulfilling at least one of the following criteria: (i) Performance status 2 (Eastern Cooperative Oncology Group [ECOG] scale), (ii) ECOG 1 and Charlson comorbidity index (CCI) ≥ 1, or (iii) age ≥ 70. Moreover, participants must have at least one measurable site of disease as defined by RECIST 1.1, as well as adequate bone marrow, hepatic and renal function. Patients having received prior immunotherapy, other investigational agents or thoracic radiotherapy within the past 5 years will be excluded from the study. Additionally, participants must not have an active or recent history of a known or suspected autoimmune disease or any other medical condition conflicting with the study interventions, and not have used immunosuppressive medication. For a full list of the inclusion and exclusion criteria see Table 1.

**Table 1 Tab1:** Complete list of inclusion and exclusion criteria

**Inclusion criteria**	
• Fully-informed written consent and locally required authorization obtained from the patient/ legal representative prior to performing any protocol-related procedures, including screening evaluations. • Age ≥ 18 years. • Histologically documented diagnosis of unresectable stage III NSCLC. • Non-feasibility of sequential chemo−/radiotherapy as determined by the site’s multi-disciplinary tumor board; if there is no tumor board, then this decision will be made by the investigator in consultation with a radiation oncologist, if the investigator is not a radiation oncologist; or by the investigator in consultation with an oncologist, if the investigator is not an oncologist. • Fulfills at least one of the following criteria: ○ ECOG 2 ○ ECOG 1 and CCI ≥ 1 ○ Age ≥ 70 years • Must have a life expectancy of at least 12 weeks. • FEV1 ≥ 40% of predicted • DLCO ≥40% of predicted • FVC or VC ≥ 70% of predicted • At least one measurable site of disease as defined by RECIST 1.1 criteria. • Adequate bone marrow, renal, and hepatic function • Female patients with reproductive potential must have a negative urine or serum pregnancy test within 7 days prior to start of trial. • Evidence of post-menopausal status or negative urinary or serum pregnancy test for female pre-menopausal patients. • The patient is willing and able to comply with the protocol for the duration of the study, including hospital visits for treatment and scheduled follow-up visits and examinations.	
**Exclusion criteria**	
• Concurrent enrollment in another clinical study or enrollment within 21 days prior to first dose of treatment, unless it is an observational (non-interventional) clinical study, or during the follow-up period of an interventional study. • Prior immunotherapy or use of other investigational agents. • History or current radiology suggestive of interstitial lung disease. • Oxygen-dependent medical condition. • Any concurrent chemotherapy, investigational product (IP), biologic, or hormonal therapy for cancer treatment. • Prior thoracic radiotherapy within the past 5 years before the first dose of study drug. • Major surgery within 4 weeks prior to enrollment into the study; patients must have recovered from effects of any major surgery. Local non-major surgery for palliative intent is acceptable. • Active or prior documented autoimmune or inflammatory disorders, with the following exceptions: Patients with vitiligo or alopecia, patients with hypothyroidism stable on hormone replacement, or any chronic skin condition that does not require systemic therapy. Patients without active disease in the last 5 years may be included but only after consultation with the study physician. • Active, uncontrolled inflammatory bowel disease. Patients in stable remission for more than 1 year may be included. • Uncontrolled intercurrent illness, including but not limited to, ongoing or active infection, symptomatic congestive heart failure, uncontrolled hypertension, unstable angina pectoris, uncontrolled cardiac arrhythmia, interstitial lung disease, gastrointestinal conditions associated with diarrhea, or psychiatric illness/social situations that would limit compliance with study requirement, substantially increase risk of incurring AEs or compromise the ability of the patient to give written informed consent. • History of another primary malignancy except for a malignancy that has been treated with curative intent and was not active for ≥5 years before the first dose of IP and of low potential risk for recurrence or adequately treated non-melanoma skin cancer or lentigo maligna without evidence of disease or adequately treated carcinoma in situ without evidence of disease • History of leptomeningeal carcinomatosis • History of active primary immunodeficiency • History of allogenic organ or tissue transplantation. • Clinical diagnosis of active tuberculosis. • Positive testing for hepatitis B virus surface antigen or hepatitis C virus RNA indicating acute or chronic infection or for human immunodeficiency virus. • Current or prior use of immunosuppressive medication within 14 days before the first dose of durvalumab. The following are exceptions to this criterion: Intranasal, inhaled, topical steroids, or local steroid injections; systemic corticosteroids at physiologic doses not to exceed 10 mg/day of prednisone or its equivalent; steroids as premedication for hypersensitivity reactions • Receipt of live attenuated vaccine within 30 days prior to the first dose of IP. • Female patients who are pregnant or breastfeeding or male or female patients of reproductive potential who are not willing to employ effective birth control. • Known allergy or hypersensitivity to any of the IPs or any of the constituents of the product. • Any co-existing medical condition that in the investigator’s judgement will substantially increase the risk associated with the patient’s participation in the study. • Patient who has been incarcerated or involuntarily institutionalized by court order or by the authorities § 40 Abs. 1 S. 3 Nr. 4 AMG. • Patients who are unable to consent because they do not understand the nature, significance and implications of the clinical trial and therefore cannot form a rational intention in the light of the facts [§ 40 Abs. 1 S. 3 Nr. 3a AMG].	

### Treatment

#### Durvalumab

Patients will be enrolled based on the in−/ exclusion criteria. Two treatment groups will be evaluated: One group will receive durvalumab immunotherapy combined with conventionally fractionated TRT (CON-group) and the other one with hypofractionated TRT (HYPO-group). In both groups, durvalumab will be administered intravenously at a fixed dose of 1500 mg on day 1 and every 4 weeks thereafter for a maximum of 12 months (maximum 13 doses, last dose at week 49) until confirmed disease progression, inacceptable toxicity, withdrawal of consent or end of the study (Fig. 1 and Table 2).

**Table 2 Tab2:** Schedule of assessments

Procedure / Point in time	Screening	Treatment Cycles (Q4W)						EOT	Post-Treatment	
	Screening	C1D1	C1D4	C2D1	C3D1	C4D1	C5D1-C13D1	EOT	Safety FU	FU (Q12W)
Informed Consent, eligibility criteria, demographics, medical and history	X									
Allocation/ Randomization	X									
Prior and Concomitant Medication Review	X	X		X	X	X	X			
Durvalumab administration		X		X	X	X	X			
Radiotherapy (CON^a^ or HYPO^b^)			X							
AEs	X	X		X	X	X	X	X	X	X
Full Physical Examination	X							X		
Directed Physical Examination		X		X	X	X	X		X	
Vital Signs, O_2_ Saturation, and Weight	X	X		X	X	X	X	X	X	
Pulmonary function tests	X			(X)^c^	(X) ^c^	together with staging		X	X	
12-lead ECG	X	Whenever clinically indicated								
ECOG Performance Status	X	X		X	X	X		X		
Pregnancy Test, CBC with Differential, Serum Chemistry Panel, Thyroid function test	X	X		X	X	X	X	X		
HBV/ HCV	X									
Urinanalysis	X	Whenever clinically indicated								
Tumor Imaging	X			(X)^d^	(X)^d^	X^e^	Q8W^e^	(X)^f^		X^g^
FACT-L and G8 screening questionnaire	X	X		X	X	together with staging		X	X	(X)^h^
Tissue	X	Optional: Re-Biopsy at time of progression								
Blood and stool	X^i^	X^i^		X		X		X		

^a^CON-group radiation scheme: Patients receive conventional fractions of 30 × 2 Gy (60 Gy) within 6 weeks of TRT to be started within 72 h after start of durvalumab treatment

^b^HYPO-group radiation scheme: Patients receive hypofractionated thoracic radiotherapy consisting of 20 × 2,75 Gy (55 Gy) within 4 weeks of TRT to be started within 72 h after start of durvalumab treatment

^c^To be performed on C2D1 and C3D1 if in accordance with local standard

^d^Chest X-ray to be performed on cycles 2 and 3 if in accordance with local standard

^e^First on-study CT imaging to be performed 12 weeks after first durvalumab administration. Further on-study imaging to be performed Q8W (56 days ±7 days)

^f^Only applicable if EOT not according to already detected disease progression

^g^In patients with EOT not due to disease progression tumor imaging will be performed until the start of a new anticancer treatment, disease progression, death, withdrawal of consent, or the end of the study

^h^Questionnaires will be collected until disease progression only and may be collected by telephone calls

^i^Biomarker sample to be taken prior to first study drug medication either during screening or C1D1 visit

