### Study endpoints

The primary endpoint of the study will be toxicity, defined by the occurrence of treatment-related pneumonitis grade ≥ 3. The ORR evaluated 12 weeks after first durvalumab administration (according to RECIST 1.1) is set as the primary efficacy endpoint. Secondary endpoints of the study comprise the occurrence of treatment-related AEs and serious AEs (SAEs), frequency of prespecified abnormal laboratory parameters, progression-free survival (PFS) and duration of clinical benefit, metastasis-free survival, overall survival (OS), and QoL.

Patient vulnerability and its association with survival and outcome will be assessed as an exploratory endpoint. To this end, the G8-screening questionnaire, a simple and fast screening tool for identifying geriatric risk profiles with a strong prognostic value for functional decline and OS in older populations with cancer, will be used [17]. Furthermore, biomaterials will be collected during the trial for correlation analyses on selected molecular parameters and clinical data in order to identify molecular biomarkers predictive for response to therapy. This approach is deemed appropriate to obtain hypothesis-generating data for future research due to the explorative character of this trial.

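### Scheduled imaging ends at any progression, so metastasis-free survival is not systematically observed after a locoregional-first progression

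*Protocol article*

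**What the plan says.** The imaging rules are in the notes to Table 2 of the protocol article (Treatment, Durvalumab). During treatment, CT is done 12 weeks after the first durvalumab dose and every 8 weeks thereafter. Durvalumab itself runs "until confirmed disease progression, inacceptable toxicity, withdrawal of consent or end of the study".

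The end-of-treatment scan is restricted by note f: "Only applicable if EOT not according to already detected disease progression". Note g then governs follow-up: "In patients with EOT not due to disease progression tumor imaging will be performed", and this continues "until the start of a new anticancer treatment, disease progression, death, withdrawal of consent, or the end of the study". Neither note separates locoregional from distant progression.

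Study endpoints lists among the secondary endpoints "metastasis-free survival, overall survival (OS), and QoL". Methods of statistical analysis says that secondary endpoints are described rather than tested. Study procedures provides survival follow-up for every patient, with telephone contact every 3 months for those who will not return. Table 2 has a 12-weekly follow-up column.

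The Background gives the reason to care about distant disease: early concomitant treatment "may particularly increase control of distant micrometastases".

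**The concern.** Metastasis-free survival, in its usual meaning, is the time to distant metastasis or death, whichever comes first. It runs on through a locoregional failure. The schedule does not. A patient whose progression is confined to the chest and who stops durvalumab for it falls outside note g and, under note f, also has no end-of-treatment scan. A patient who stopped for another reason and then progresses locally leaves imaging at that point. In both cases a later metastasis is recorded only if it happens to be reported, while death is still recorded.

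The analyst then has two choices: censor at the local progression, or carry the patient forward and count only death. Either can make distant control look better than it is, on the listed endpoint closest to the distant-control rationale. An analysis plan can choose between the two, but it cannot supply observations that nobody was scheduled to make.

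**Working it through.** **The plan's own figures.** The article states none for metastasis-free survival. Its response-rate and safety designs do reproduce (two-stage exact type I error 0.0954 and power 0.8001; lead-in probabilities 0.776 and 0.870), but they do not bear on this point.

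**Which patients still have scheduled scans**

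| Situation | Later scheduled scan? | Source |
|---|---|---|
| On durvalumab, no confirmed progression | Yes, every 8 weeks after week 12 | note e |
| Treatment ended for progression, local or distant | No | notes f and g |
| Treatment ended for another reason, no progression yet | Yes, while none of the note g stopping events has occurred | note g |
| The same patient after a local-only progression | No | note g |

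Rows 2 and 4 are the gap.

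**Illustration of size.** The documents give no event rates, so every input here is an assumption. Monthly hazards: distant metastasis D = 0.03; death without metastasis K = 0.01; local-first progression L = 0.02 or 0.04; death after metastasis 0.08. Local progression multiplies D and K by m = 1, 2 or 3. Let h = D + K = 0.04 and the horizon be 24 months.

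- Share with local progression first: L/(L+h) × (1 − exp(−24(L+h))). For L = 0.02 this is 0.333 × (1 − exp(−1.44)) = 0.254. For L = 0.04 it is 0.5 × (1 − exp(−1.92)) = 0.427. With 44 patients per arm that is 44 × 0.254 = 11 to 44 × 0.427 = 19 patients.
- True value: exp(−24(h+L)) + ∫₀²⁴ L exp(−(h+L)u) exp(−mh(24−u)) du. For L = 0.02 and m = 2: 0.237 + 0.090 = 0.327.
- Censoring at local progression: the Kaplan-Meier curve estimates exp(−24h) = exp(−0.96) = 0.383, whatever m is.
- Counting only deaths after local progression: replace exp(−mh(24−u)) in the integral by the probability of being alive 24−u months after local progression, with or without an unseen metastasis. With s = 24−u this is exp(−mhs) + mD × [exp(−0.08s) − exp(−mhs)]/(mh − 0.08). At m = 2, where mh = 0.08, the second term becomes mDs exp(−mhs).

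| L | m | True | Censored (excess) | Deaths only (excess) |
|---|---|---|---|---|
| 0.02 | 1 | 0.383 | 0.383 (0.00) | 0.425 (0.04) |
| 0.02 | 2 | 0.327 | 0.383 (0.06) | 0.387 (0.06) |
| 0.02 | 3 | 0.297 | 0.383 (0.09) | 0.365 (0.07) |
| 0.04 | 1 | 0.383 | 0.383 (0.00) | 0.455 (0.07) |
| 0.04 | 2 | 0.287 | 0.383 (0.10) | 0.389 (0.10) |
| 0.04 | 3 | 0.237 | 0.383 (0.15) | 0.350 (0.11) |

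A simulation of 400,000 patients per row agrees with these values to within about 0.002.

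For scale, with complete follow-up of 44 patients the standard error of a proportion of 0.383 is √(0.383 × 0.617/44) = 0.073. Under these assumptions the excess runs from nothing to about twice the sampling error.

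**The case against.** Four points on the other side deserve weight.

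- **The definition is not shown.** The article names the endpoint without defining it. If the full protocol means distant metastasis as first failure, the schedule already supports it and only the name misleads. This stands as a limit. It is also why one of the two remedies is simply to report that quantity.
- **Censoring need not bias.** At m = 1 the censored estimate is exact, so a reader who infers that the endpoint is overstated whatever rule is used goes too far. Censoring overstates it only if local failure raises later risk.
- **The endpoint is secondary and descriptive.** The response-rate tests are separate for each arm, and no formal comparison of distant control is planned. Describing an estimate does not remove its bias, but the consequence is limited.
- **Scans may run past a first progression.** Treatment continues to confirmed progression, so on-treatment imaging can outlast a first, unconfirmed one. This narrows the gap but does not close it.

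Two stronger readings are tempting. A reader might infer that PFS is also unmeasurable. It is not: progression is the PFS event, so stopping there loses nothing. Only patients who start new therapy before progressing are affected, and ending assessment at that point is a common convention. On an assumed progression hazard of 0.07 per month, with 2% to 8% switching first, the error in 12-month PFS is about 0.03 or less. A reader might also infer from the row "Prior and Concomitant Medication Review", blank after the last cycle, that new anticancer therapy goes unrecorded. The table does not show that. Note g needs the start date, and the case report form may collect it elsewhere.

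**Conclusion.** The point holds for metastasis-free survival alone. As printed, the schedule makes no systematic search for distant disease once a locoregional progression has ended treatment or post-treatment imaging. What it observes well is distant metastasis as first failure.

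Counting only later deaths overstates metastasis-free survival whenever some of these patients metastasise before dying. Censoring at local progression overstates it if local failure raises later risk. The actual size cannot be derived from the article. The excess of 0 to 0.15 at 24 months rests wholly on the assumed hazards, and on no metastasis being reported from routine care after local progression; any that are reported would shrink it.

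The primary toxicity endpoint, the 12-week response rate, the stopping rules and the sample size are untouched.

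**What to change.** Make the reported endpoint match what is observed, in one of two ways.

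1. **Collect the date.** After a locoregional-only progression, use the existing 12-weekly follow-up contacts to ask whether routine-care imaging has shown distant metastasis, and record its date, until metastasis or death. No protocol scan is added. The cost is one follow-up form item and some site effort. Routine scans are less regular than scheduled ones, so dates will be coarser and some metastases will be found late.
2. **Report the narrower quantity.** Replace metastasis-free survival by the cumulative incidence of distant metastasis as first failure, with locoregional failure and death as competing events. This needs no new data, provided the site of first progression is recorded. The cost is that it says nothing about distant disease after local failure.

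The first option keeps the endpoint closest to the distant-control rationale. The second is sufficient if the sponsor wants no further data collection.
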